**Method/design:**

This study is a single-center, double-blinded, randomized, placebo-controlled, parallel-group trial. A total of 120 patients will be randomly allocated in a 1:1 ratio to receive either *P. grandiflorum* granules or placebo granules twice daily for 12 weeks. The primary outcome is heart failure (either clinical or subclinical). The secondary outcomes include all-cause mortality, cardiac death, electrocardiogram (ECG) findings, left ventricular diastolic function, longitudinal systolic strain and velocities measured by tissue Doppler imaging, cardiac biomarkers, such as troponin I (TnI), brain natriuretic peptide (BNP), and creatine kinase isoenzymes (CK-MB). Assessments will be performed at baseline (before randomization) and 3, 6, 9, 12, 16, and 20 weeks after randomization.

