### Outcomes

#### Primary outcome

The primary outcome is heart failure (either clinical or subclinical). In this study, New York Heart Association (NYHA) Functional Classification will be used to evaluate the extent of clinical heart failure. Left ventricular ejection fraction (LVEF) less than 50% or a drop of more than 15% from baseline is defined as subclinical heart failure in this study. Ejection fraction is measured using multigated acquisition (MUGA) scan in all participants. MUGA scans will be performed by the same physician; this physician is not involved in recruitment of the study.

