#### Secondary outcomes

Secondary outcomes include all-cause mortality, cardiac death, electrocardiogram (ECG) findings, left ventricular diastolic function, longitudinal systolic strain and velocities measured by tissue Doppler imaging, cardiac biomarkers, such as troponin I (TnI), brain natriuretic peptide (BNP), and creatine kinase isoenzymes (CK-MB) [23].

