### Statistical analysis

An independent, professional statistician will perform the data analysis for the results and the AEs. Intention-to-treat (ITT) analysis will be carried out in all participants who complete the clinical trial. Missing data will be adjusted for using the last observation carried forward (LOCF) principle to obtain a complete database. Continuous data will be presented as means and standard deviations $$ \left(\overline{X}\pm SD\right) $$, or medians and quartiles. The comparability of the two groups will be assessed using the independent samples *t* test for continuous variables and the chi-square (χ^2^) test or Wilcoxon test, when appropriate, for categorical variables. The cumulative dose of anthracycline to cause cardiotoxicity will be estimated in each group using Kaplan-Meier curves; differences between the curves will be assessed using the log-rank method. The crude and adjusted hazard ratios and 95% confidence intervals will be estimated using a Cox proportional hazards regression model. All analyses will be performed using IBM SPSS software version 19 (IBM, Armonk, NY, USA). A two-tailed *P* value <0.05 was set for statistical significance.

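### The only test named for continuous variables is an unadjusted t test, and nothing stated uses the baseline value or repeated visits for the continuous secondary cardiac measures

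*Protocol article*

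**What the plan says.** The abstract of the protocol article gives the visit plan: "Assessments will be performed at baseline (before randomization) and 3, 6, 9, 12, 16, and 20 weeks after randomization". The Secondary outcomes section lists several measures that are continuous by nature: "left ventricular diastolic function, longitudinal systolic strain and velocities measured by tissue Doppler imaging, cardiac biomarkers, such as troponin I (TnI", together with BNP and CK-MB.

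For continuous variables the Statistical analysis section names a single test: "The comparability of the two groups will be assessed using the independent samples" *t* test. Categorical variables get a chi-square or Wilcoxon test. On incomplete data it says "Missing data will be adjusted for using the last observation carried forward (LOCF) principle to obtain a complete database". The significance rule is general: "A two-tailed *P* value <0.05 was set for statistical significance".

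The remaining methods are for events. Kaplan-Meier curves and the log-rank test are applied to the cumulative anthracycline dose at which cardiotoxicity occurs, and "The crude and adjusted hazard ratios and 95% confidence intervals will be estimated using a Cox proportional hazards regression model". The primary outcome is itself an event, clinical or subclinical heart failure. Its subclinical part is a threshold: "Left ventricular ejection fraction (LVEF) less than 50% or a drop of more than 15% from baseline is defined as subclinical heart failure".

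**The concern.** A patient's strain, diastolic function or biomarker level at follow-up is partly predicted by the same patient's value before treatment. A two-sample t test on follow-up values leaves that predictable part in the error term. It also takes each visit in isolation. LOCF then fills later gaps with an earlier value, whereas a repeated-measures model would use a patient's observed visits directly.

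Scale is a second issue. The article allows for continuous data that are better summarised by medians and quartiles, so it expects some skew. Yet it attaches the Wilcoxon test to categorical variables and gives continuous variables only the t test. Read literally, a skewed biomarker could be described by its median and tested on its mean.

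At stake is the precision of the secondary cardiac comparisons in a trial of 120 patients that is also meant to inform a larger one. The baseline measurements that would recover this precision are already planned.

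**Working it through.** **Inputs from the protocol article**

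- Sample size calculation section: 60 patients per group and 20% anticipated dropout.
- Statistical analysis section: two-sided 0.05.
- Randomization section: 1:1 allocation.

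**Assumed inputs**

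- Power of 80%, used as a yardstick.
- Correlation ρ between baseline and follow-up of 0.3, 0.5 or 0.7. The article gives no correlation and no SD, so differences are in SD units of the follow-up value.

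**The plan's own figure.** The article states no effect size, event rate, SD or power, so 120 cannot be derived. Only the dropout step can be checked: 60 × (1 − 0.20) = 48 completers per group, and 48 / 0.80 = 60.

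**Unadjusted t test, one follow-up visit (normal approximation)**

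Detectable difference = (z₀.₉₇₅ + z₀.₈₀) × √(2/n) = (1.960 + 0.842) × √(2/48) = 2.802 × 0.2041 = 0.572 SD.

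**Baseline-adjusted comparison (ANCOVA), same visit**

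Adjustment multiplies the variance of the arm difference by 1 − ρ², and so the detectable difference by √(1 − ρ²). The equivalent sample size per group is 48 / (1 − ρ²).

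| ρ (assumed) | 1 − ρ² | Variance cut | Detectable difference, n = 48 | Equivalent n per group | Power at an assumed 0.5 SD |
|---|---|---|---|---|---|
| unadjusted | 1 | – | 0.572 SD | 48 | 68.8% |
| 0.3 | 0.91 | 9% | 0.572 × 0.954 = 0.546 SD | 52.7 | 72.8% |
| 0.5 | 0.75 | 25% | 0.572 × 0.866 = 0.495 SD | 64.0 | 80.7% |
| 0.7 | 0.51 | 49% | 0.572 × 0.714 = 0.408 SD | 94.1 | 92.9% |

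**If all 60 per group are analysed.** The unadjusted detectable difference is 2.802 × √(2/60) = 0.511 SD. With adjustment it is 0.488, 0.443 or 0.365 SD for ρ of 0.3, 0.5 or 0.7.

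**Would a t test on change from baseline do instead?** With equal variances at the two times, the variance of a change relative to a follow-up value is 2(1 − ρ): 1.4, 1.0 and 0.6 for the three correlations. ANCOVA gives 0.91, 0.75 and 0.51, which is smaller each time. At ρ = 0.3 the change score is worse than ignoring baseline altogether.

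**The case against.** The strongest objection is that the quoted sentence may not concern outcomes at all. Comparability of two groups usually means balance at entry. The sentence names no outcome and no visit, and it comes before the sentences on the event analysis. A reader might infer that the cardiac measures will be compared only by unadjusted t tests. The text does not say that, and the point is therefore put conditionally.

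On the baseline reading, what is left is that no analysis is described for the continuous secondary outcomes. A journal article may leave that to a full protocol or SAP, neither of which is shown, so the absence alone is no fault. What stands is narrower: the t test is the only method the article states for continuous data, its scope is unclear, and a better method is available for the data being collected.

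Three further inferences should be resisted:

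- **That the primary analysis is flawed on this account.** The primary outcome is an event, and a Cox model with crude and adjusted hazard ratios is already planned.
- **That a large, countable number of false-positive tests follows.** Such a count needs every measure to be taken and tested at every visit. The schedule figure is not shown, and tests on the same patients are not independent.
- **That P values for baseline comparability, or the unlisted Cox covariates, are part of the problem.** Baseline P values change no treatment estimate, and naming a covariate only fills in a detail.

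The objection is also right that the size of the gain rests on assumed correlations. At 0.3 the gain is small.

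**Conclusion.** The concern holds in conditional form and for the secondary outcomes only. If the t test is meant for follow-up values of the continuous cardiac measures, it is an inefficient choice. A baseline-adjusted analysis would cut the variance of each single-visit comparison by between 9% and 49%, using data already planned.

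That range depends on an assumed correlation of 0.3 to 0.7, applied alike to imaging measures and biomarkers, and on the usual large-sample variance formula. The true gain may differ between measures. The t test would remain a valid comparison of randomised groups, so the issue is lost precision rather than bias from the test itself. If the t test is meant for baseline balance only, no outcome analysis needs replacing and a clarifying sentence with the intended model is enough.

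**What to change.** In the Statistical analysis section, or in the SAP if one exists:

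1. State that the independent-samples t test is not the analysis of follow-up outcomes.
2. For each continuous secondary cardiac measure (diastolic function, strain and velocities, TnI, BNP, CK-MB), specify a baseline-adjusted model. One option is a mixed model for repeated measures with baseline value, arm, visit and arm-by-visit terms, fitted to observed data without LOCF. The other is ANCOVA at week 12.
3. Analyse skewed biomarkers on the log scale.
4. Report the week-12 arm difference with its 95% confidence interval as the main contrast for each measure, and the other visits as descriptive. Week 12 is the end of the intervention period and the time point in the article's hypothesis. Confirm against the visit schedule that each measure is taken then.

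The cost is a change of analysis wording. It needs no new visits, measurements or patients. It should be settled before treatment codes are opened.

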## Discussion

Since *P. grandiflorum* has never been studied for the prevention of cardiotoxicity in patients receiving anthracycline-based chemotherapy, we performed a randomized controlled trial to evaluate the cardioprotective effects and safety of *P. grandiflorum* in patients with early breast cancer receiving anthracycline-based chemotherapy. We also plan to assess the feasibility of a future, larger-scale clinical trial. Despite having no precedent of a clinical trial assessing our intervention, this protocol adheres to strict, high-quality methodology and follows the Consolidated Standards of Reporting Trials (CONSORT) statement for RCTs of herbal medicines [25] and the SPIRIT 2013 statement [26]. Key elements for performing a high-quality RCT have been described above in detail, such as randomization, allocation concealment, blinding methods, sample size, intervention, outcome measures, and statistical analysis. There are some limitations to our study. First, patients with breast cancer have longer overall survival (OS) and progression-free survival (PFS) than patients with other kinds of cancer. Since the follow-up period of this study is relatively short, we may not be able to compare OS and PFS between the two groups. Second, the gold standard for diagnosing anthracycline-induced cardiotoxicity is endomyocardial biopsy (EMB). However, EMB carries risk of serious complications and thus EMB is limited in its clinical application. Surrogate markers of cardiotoxicity may be easier to perform and carry lower risk, but also may result in more false-positive or false-negative results in both groups.

### Trial status

Participant recruitment and randomization began in November 2016. Recruitment is ongoing.

## Abbreviations

AE: Adverse event
ANT: Anthracycline
BNP: Brain natriuretic peptide
CAD: Coronary artery disease
CFDA: China Food and Drug Administration
CHM: Chinese herbal medicine
CK-MB: Creatine kinase isoenzymes
CONSORT: Consolidated Standards of Reporting Trials
CRF: Case report form
DNR: Daunorubicin
DOX: Doxorubicin
DSMB: Data and Safety Monitoring Board
EMB: Endomyocardial biopsy
ECG: Electrocardiogram
EPI: Epirubicin
GCP: Good Clinical Practice
ITT: Intention-to-treat
KPS: Karnofsky Performance Status
LOCF: Last observation carried forward
LVEF: Left ventricular ejection fraction
MUGA: Multigated acquisition
NO: Nitric oxide
NYHA: New York Heart Association
OS: overall survival
PFS: Progression-free survival
RCT: Randomized controlled trial
ROS: Reactive oxygen species
SAE: Serious adverse event
SPIRIT: Standard Protocol Items, Recommendations for Interventional Trials
TCM: Traditional Chinese medicine
TnI: Troponin I
